**Methods:**

The total 122 patients undergoing elective upper extremity surgery will be randomly allocated to receive either an IA-SB or a CA-SB using a double-injection (DI) technique. In the IA-SB group, a portion of LA (15 mL) is injected accurately to the intertruncal plane between the middle and lower trunks under real-time ultrasound guidance; then, the remaining volume (10 mL) is carefully distributed to the other intertruncal plane between the upper and middle trunks. In the CA-SB group, the DI technique will be carried out as described in Tran’s study. The primary outcome is the percentage of patients with a complete sensory blockade at 20 min with a predefined non-inferiority margin of − 5%. The secondary outcomes include the sensory-motor blockade of all 4 terminal nerves, onset times of the individual nerves within 30 min, block-related variables, and adverse events.

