### Sample size calculation and statistical analysis

Our working hypothesis is that ultrasound-guided CA- versus IA-SB yield similar block dynamics. Thus, this study will be designed as a non-inferiority trial. In the previous studies using single or multiple injections in SB, we have observed that the proportion of patients with complete sensory blockade reached a plateau starting at 20 min after injection. It fluctuates between 70% and close to 100% within 30 min [3–6, 16]. In other words, relative to itself, the variation is very subtle from 20 to 30 min. The primary outcome is considered as the proportion of patients with complete sensory blockade of all 4 terminal nerves at 20 min after injection in this study. Based on a pilot study with 15 patients in each group, the proportion of patients with complete sensory blockade achieved was 73% in the CA-SB group and 87% in the IA-SB group (unpublished data). Therefore, we assume that a difference in proportion between the two groups less than − 5%, measured at 20 min after injection, will be considered non-inferiority. The required sample size per group is calculated to be 55 with a statistical power of 80% and a one-sided 95% confidence interval. To account for a possible 10% dropout rate, the total sample size is inflated to 122 participants (*n* = 61, per group).

Statistical analysis will be performed using *SPSS for Windows 18.0* (SPSS Inc., Chicago, IL). For continuous data, normality will be first assessed with the *Kolmogorov-Smirnov test* and then analyzed using an *independent-samples t test.* Categorical variables will be summarized as a frequency, *n* (%), such as the proportion of complete sensory or motor blockade, success rates, and adverse events, etc. The *Pearson χ*^*2*^
*test*, *Fisher’s exact test*, or a *Mann-Whitney U test* will be used for categorical variables as appropriate. A *p < 0.05* will be considered statistically significant for all results.

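### The analysis paragraph covers complete sensory blockade only with tests of no difference at p < 0.05, and never says that a confidence limit will be compared with the −5% margin

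*Protocol article*

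**What the plan says.** All of this is in the protocol article, mostly in the section on sample size calculation and statistical analysis.

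- **Design.** "Thus, this study will be designed as a non-inferiority trial". The hypothesis behind it reads: "Our working hypothesis is that ultrasound-guided CA- versus IA-SB yield similar block dynamics".
- **Primary outcome.** "The primary outcome is considered as the proportion of patients with complete sensory blockade of all 4 terminal nerves at 20 min" after injection.
- **Margin.** The Methods part of the Abstract gives "complete sensory blockade at 20 min with a predefined non-inferiority margin of − 5" per cent. The sample-size paragraph states the criterion as "a difference in proportion between the two groups less than − 5%, measured at 20 min after injection, will be considered non-inferiority".
- **Sizing.** 55 per group for 80% power and a one-sided 95% confidence interval, raised to 61 per group (122 in total) for 10% dropout. The pilot rates are 73% (CA) and 87% (IA).
- **Analysis.** Categorical variables are summarised as frequencies, "such as the proportion of complete sensory or motor blockade, success rates, and adverse events, etc". The Pearson chi-square test, Fisher's exact test or the Mann-Whitney U test "will be used for categorical variables as appropriate". A p value below 0.05 "will be considered statistically significant for all results".

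The analysis paragraph mentions neither the margin nor a confidence interval, and it does not set the primary outcome apart.

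**The concern.** The three named tests, as described, have zero difference as their null hypothesis. The trial's question has a different null: that IA is worse than CA by 5 points or more. The one-sided interval that would answer it appears only in the sample-size sentence. The sentence with the margin names a difference in proportions but no confidence limit, so it could be read as a rule on the point estimate.

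An analyst who follows the analysis paragraph as written would therefore report a p value for the primary measure that does not address the margin. When that p value exceeds 0.05, the primary conclusion is left undecided. With a hypothesis worded as similarity, there is then a risk that the missing difference is taken as the answer.

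**Working it through.** **Inputs.** From the sample-size paragraph: CA 73%, IA 87%, margin −5 points, one-sided 95% interval (z = 1.645), 80% power (z = 0.842), 55 per group before dropout and 61 after.

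**Step 1: reproduce the plan's sample size.** The distance from the assumed difference to the margin is 0.87 − 0.73 + 0.05 = 0.19.

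- Unpooled variance: n = (1.645 + 0.842)² × (0.73×0.27 + 0.87×0.13) / 0.19² = 6.18 × 0.3102 / 0.0361 ≈ 53.1, so 54.
- Pooled variance (mean rate 0.80): n = 6.18 × 2×0.80×0.20 / 0.0361 ≈ 54.8, so 55, as stated.
- Dropout: 55 × 1.1 = 60.5, so 61, as stated.

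The stated size is thus a non-inferiority calculation at one-sided 0.05.

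**Step 2: define the two rules at 55 per arm.** Let d = IA proportion − CA proportion, and let p̄ be the mean of the two.

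- Test of no difference: z = d / √(2p̄(1−p̄)/55), significant if |z| > 1.96 (uncorrected Pearson).
- Confidence-limit rule: L = d − 1.645 × √([p_CA(1−p_CA) + p_IA(1−p_IA)]/55), non-inferior if L > −0.05. A Wald limit is used for illustration; the protocol names no interval method.

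**Step 3: two possible results with almost the same p value.**

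| CA | IA | d | Pearson p | L | Non-inferior? |
|---|---|---|---|---|---|
| 44/55 | 38/55 | −10.9 points | 0.19 | −24.5 points | no |
| 40/55 | 46/55 | +10.9 points | 0.17 | −1.9 points | yes |

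Both are non-significant, and they lead to opposite conclusions on the margin.

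**Step 4: how often this happens.** Exact binomial probabilities, summed over all tables at 55 per arm:

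| True CA, IA | p > 0.05 | p > 0.05, non-inferiority not shown | p > 0.05, non-inferiority shown | Limit rule passes |
|---|---|---|---|---|
| 73%, 73% | 0.950 | 0.822 | 0.129 | 0.153 |
| 73%, 87% (planning) | 0.540 | 0.183 | 0.356 | 0.817 |
| 73%, 68% (at the margin) | 0.911 | 0.864 | 0.047 | 0.053 |

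At 61 per arm the picture is the same: 0.814 in place of 0.822, 0.354 in place of 0.356, and power of the limit rule 0.852 in place of 0.817.

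**Step 5: significant results.** No table at 55 per arm has z > 1.96 in favour of IA together with L at or below −5 points, and none has z < −1.96 together with L above −5 points. Only non-significant results leave the margin undecided.

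**The case against.** The strongest defence is that the margin criterion is already stated, in the Abstract and again in the sample-size paragraph of the same section, next to a one-sided 95% interval. The sentence naming the blockade proportion is about descriptive summary, and its wording resembles the row for sensory or motor blockade under other secondary outcomes in Table 1. The test sentence is generic. On this view the paragraph is standard text for group comparisons, and the primary analysis follows from the margin; an analysis plan not shown may spell it out.

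Part of this stands. The non-inferiority framework is in the document, and the text does not prove that the conclusion will be drawn from a chi-square test. The interval method may well be left to the analysis plan. But the paragraph does more than stay silent. It names a test family for categorical variables, the primary measure is one of these, and its threshold covers all results without exception. The qualifier on the tests chooses among three procedures, none of which, as described, uses the margin. An analysis plan that applied the margin would have to depart from this text.

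Three stronger readings are tempting and are not supported:

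- *That p > 0.05 will be read as similarity.* The document never says so. It is a risk raised by the wording of the hypothesis, and the 91% of non-significant results at the margin is not a false-claim rate of the plan.
- *That the plan fails to deliver its power, because chi-square favours IA in only 46% of trials at the planning rates.* This would need p < 0.05 to be the success criterion for non-inferiority, which is not stated either. Under the limit rule the power is 0.82.
- *That a significant result says nothing about the margin.* Step 5 shows otherwise at this sample size.

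**Conclusion.** The concern holds as a mismatch within one section: a −5% criterion and a one-sided interval for sizing, but an analysis paragraph that offers only tests of no difference at p < 0.05 and no comparison of a confidence limit with the margin. Its weight comes from non-significant results, which are common: about 54% of trials at the planning rates and 95% with equal rates of 73%. Among all trials, about 82% at equal rates are non-significant without showing non-inferiority, and about 36% at the planning rates are non-significant while showing it.

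These figures assume 55 evaluable patients per arm, an uncorrected Pearson test at two-sided 0.05 and a Wald limit; another interval method would shift them somewhat. The sample size, margin and alpha are not called into question by this point. It matters because it bears on the trial's primary conclusion.

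**What to change.** Add a sentence on the primary analysis: the IA minus CA difference in the proportion with complete sensory blockade at 20 min is reported with its one-sided 95% lower confidence limit (the lower limit of the two-sided 90% interval), and non-inferiority is declared only if that limit lies above −5 points. Reword the criterion in the sample-size paragraph to match, so that it refers to the confidence limit and states the direction of the difference. Restrict the Pearson, Fisher and Mann-Whitney tests, and the p < 0.05 threshold, to the secondary outcomes.

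Naming the interval method and adding a superiority test after non-inferiority is shown are optional. If the analysis plan already contains the limit rule, it is enough to bring the protocol text into line with it. The cost is a few sentences and a few lines of code; sample size, data collection and conduct do not change.

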### Data collection and retention

The nerve block-related parameters and postoperative follow-up data will be recorded by a research assistant, and a statistics analysis will be carried out by an independent statistician. To enable examination and re-analysis from regulatory authorities, all electronic data will be desensitized and stored securely at the Department of Anesthesiology of the Third Affiliated Hospital of Sun Yat-sen University for 5 years. Preserved paper materials of this study include the original signed informed consents, study protocol and interventions, and case report forms. The project will be monitored by a data monitoring committee composed of specialists in ethics, anesthesiology, and statistics. These data will be kept in our research database and not revealed to other people without appropriate permission.

### Adverse events

All adverse events will be monitored and recorded. Once any serious adverse event occurs, it will be immediately reported to the research group, which will determine the causality and therapeutic measures of the adverse events. The chief investigator will be responsible for reporting all adverse events to the Ethics Committee.

### Auditing

No formal auditing process is proposed for this trial.

### Protocol amendments

In principle, the established study protocol is not to be modified. Any amendments to the study will be first initiated by the principal investigators and then agreed and confirmed by all study participants. Finally, the modified version of the protocol will be submitted to the Ethics Committee for approval.

### Trial dissemination

The research results and findings will be disseminated in a peer-reviewed journal or at scientific conferences.

### Patient and public involvement

No patients were involved in the design, recruitment, and conduct of the study and were also directly consulted in the development of the research question or outcome measures. An original article will be prepared to present the trial results at the proper time after the end of the study. Results of the final study will be disseminated to all study participants through E-mail recorded at the time of enrolment. The burden of intervention will not be taken by the participants themselves.

## Discussion

The supraclavicular brachial plexus block does gain popularity benefited from the application of ultrasonic visualization technology [17, 18]. However, the optimal needling technique for the SB is remaining controversial. Various studies have proposed a series of techniques of where to first inject the LA and how many injections to perform around the brachial plexus, which include single-, double-, triple-, targeted intracluster-, or modified-injection techniques for the last nearly two decades [3–6, 9, 11, 16]. Up to now, the most common techniques for LA injection described at the first rib level are a single or double injection. The needle intentionally breaches the layer located at the outer border of the entire plexus, and the needle tip is observed as it advances to the “corner pocket” (at the intersection of the first rib and subclavian artery) in real time for a single injection [19]. If a double injection is used, then the needle will be redirected and placed in the middle of hypoechoic structures representing neural tissue [3]. However, these techniques have been proved to be associated with a high risk of intraneural injection. A recent cadaver study has reported that sub-perineural injections can be as high as 24% for a single intracluster injection [20]. As a result, it should be remembered that it cannot exclude direct or indirect nerve injuries even under real-time imaging of the needle-nerve distance [21, 22]. Therefore, in clinical practice, it is eager to carry out a scheme to prevent nerve injuries and finding a more appropriate injection site will be better and safer according to the needs of inexperienced operators.

The development of a new-style approach or needling technique is coming into clinical practice because the advancement in ultrasound guidance allowed for a further understanding of the underlying anatomy of the brachial plexus (trajectory and surrounding fascial sheath) [23]. For instance, the selective trunk block which is a novel brachial plexus block technique is just inspired by accurately identifying the main components of the plexus above the clavicle under real-time visualization and is expected to result in producing surgical anesthesia of the whole upper extremity [24, 25]. Recently, Siddiqui and colleagues [12] have proposed an alternative approach to the classical approach to a SB, in which LA is carefully injected into the investing adipose layers between the trunks. This is a very promising needling technique without intraneural injection for ultrasound-guided SB. However, the specific data of block dynamics is not yet clear compared with the classical approach. The objective of this study was to assess the block dynamics and clinical feasibility with DI in the supraclavicular fossa via IA.

In the previous technique-related trials, the more needle passes seem the shorter onset time and better sensory-motor blockade [7]. However, the shorter onset time associated with the incremental needle passes is counterbalanced by its longer performance time and is accompanied with a high risk of intraneural injection [3–6, 16]. Nonetheless, the most used and teaching needling technique is the DI technique because, with an acquired satisfactory learning curve, the trainees can implement relatively safe skills while retaining the benefit of quick onset [26, 27]. In addition, we also observed that, in many patients, rather than being a singular entity, the neural cluster is composed of more than one main satellite clusters after the first injection [6, 8]. Finding a better approach for better LA diffusion based on the advancement in ultrasound guidance might be a meaningful technological innovation. Excitingly, the novel IA is just performed between the epineurium of the 3 trunks, and it aims to anesthetize the brachial plexus where the 3 trunks can be visualized as independent of hypoechoic nodules [12]. The authors have proposed that this approach can provide complete blockade of all 4 terminal nerves and satisfying onset times while avoiding intraneural injection and pleural puncture. In our study, the sensory-motor blockade-related clinical parameters including the percentage of patients with complete blockade at all the predetermined intervals, onset times, and adverse events will be recorded. As the IA is closer to the interscalene, an important issue concerning the potential risks of diaphragmatic paralysis is another important dimension of safety [28, 29]. The excursion of the ipsilateral hemidiaphragm will be measured by M-mode ultrasonography in supine position via the anterior subcostal route in centimeters at 35 min after injection [30]. We will also observe the duration of sensorimotor block and potential nerve injury after surgery. The results can help us to determine the efficacy and safety of an IA with the DI technique.

In conclusion, this trial should enable us to better assess the effectiveness of an IA to ultrasound-guided SB, with the potential possibility of avoiding intraneural injection. It may provide us with an ideal inserting approach for optimized risk-benefit at the supraclavicular fossa. It should also advance the understanding of the optimal site of injection and optimization of the diffusion of LA in this inserting approach with the DI technique.

## Trial status

The study will be conducted over a period of more than 9 months (from 26 November 2020 to 31 August 2021) with the latest version of the protocol. At the time of manuscript submission, candidates had been included and some patients had participated in the study.

## Data Availability

All investigators will have access to the final de-identified study dataset from the corresponding author for the purpose of scientific publications.

## Abbreviations

IA: Intertruncal approach
CA: Classical approach
SB: Supraclavicular block
LA: Local anesthetic
DI: Double injection
ASA: American Society of Anesthesiologists
CONSORT: Consolidated Standards of Reporting Trials
SPIRIT: Standard Protocol Items: Recommendations for Interventional Trials
